### Eligibility criteria {10}

To be eligible for inclusion, patients need to satisfy all the following criteria:
Age ≥ 18 yearsAcute syndrome due to presumed acute stroke, defined by a FAST score of 2 or 3 with an arm motor deficit, and a time ≤ 2 h from last seen wellSystolic BP ≥150 mmHg(recorded twice)Able to provide brief informed consent (if waiver of consent is not approved by the relevant ethics committee)

Patients will not be eligible if there is one or more of the following:
Coma—no response to tactile stimuli or verbal stimuli (e.g., Glasgow coma score < 5)Known severe co-morbid disease (e.g., cancer, chronic airflow disease, severe dementia, severe heart failure, pre-stroke disability [i.e., needing help with daily activities])History of epilepsy or seizure at the onset of symptomsHistory of recent head injury (< 7 days)Hypoglycemia (glucose < 2.8 mmol/L)

In each case, the decision about a patient’s eligibility will be based on the interpretation of these criteria by participating ambulance staff.

### What is the consent process? {26a}

Each participating site must obtain written approval(s) from their hospital research ethics committee (EC) (e.g., institutional review board [IRB]), and any other relevant regional or national body, before patient recruitment commences. A two option, mixed consent process is the proposed method for use in the study, according to local/national rules and regulations.

Option 1: (a) Waiver of consent for administration of study intervention in the ambulance and (b) consent for use of medical data and follow-up of patients obtained in hospital.

Reasons why waiver of consent is requested for this study are outlined below.
Ambulance staff have limited time to obtain consent during their assessment, retrieval, and rapid transport of a patient to the hospital. Taking additional time to obtain informed consent could delay a patient’s arrival at hospital, and potentially compromise their management and outcome.Stroke is a critical illness, with a proven limited time window for reperfusion treatments to benefit a patient with IS and a hypothesized limited time window for BP moderating treatments to benefit a patient with ICH. The trial is assessing the benefits of rapid BP lowering treatment initiated as soon as possible after the onset of symptoms. Taking additional time to obtain informed consent can delay the initiation of treatment and reduce potential benefits to the patient.Many patients with acute stroke do not have cognitive capacity to provide informed consent, due to impaired consciousness, aphasia, or confusion. Limiting participation only to patients with mild symptoms reduces the ability to assess the treatment in a broad range of patients, and in particularly those with more severe illness who have the greatest potential to benefit from reducing initial and secondary brain injury after ICH and/or IS.Waiver of consent is often applied in the prehospital setting for other similar critical illnesses, such as cardiac arrest, head injury, and status epilepticus.The requirement for consent may compromise the relationship between the ambulance staff and patient/family, create suspicion/concern and/or refusal to receive standard care, and potential to worsen patient outcomes.The study intervention is low risk, as the recommended BP lowering agent—urapidil—is readily available in clinical practice and is being used within its licensed indication to treat acute hypertension. Urapidil has a well-accepted low adverse event profile, with the most common side-effect of hypotension being readily corrected through its discontinuation and the use of intravenous (IV) fluid replacement, for which ambulance staff are well trained in its management. The administration of urapidil is by trained and accredited ambulance-assigned doctors, and all adverse events will be systematically reported to, and monitored by, project staff; and reported and reviewed by an independent Data Safety Monitoring Board (DSMB). The BP monitoring protocol has been well tested in patients with acute stroke presenting to hospital, including those with acute ICH and IS, where the small risk of harms being well defined.

Option 2: (a) Brief (limited) informed consent in ambulance (if waiver of consent is not approved by the EC) followed by (b) consent for use of medical data and follow-up of patients obtained in hospital.

A brief consent will be obtained at the stroke scene or in the ambulance, where four simple items will be contained in the consent form and explained by the ambulance doctor to the patient: (i) they are suspected to have acute stroke, (ii) their BP may benefit from lowering as early as possible, (iii) that IV bolus of a drug to lower the BP or usual treatment without ambulance BP lowering will be applied, and (iv) do they agree to take part in a research study. If the patient is not fully competent to give informed consent (e.g., aphasia or reduced level of consciousness), the patient’s next-of-kin or surrogate will be approached to sign this consent form on his/her behalf.

If brief (limited) informed consent in the ambulance is approved by local EC, for noncompetent patients for whom there is no next-of-kin present to provide informed consent, further approval will be sought to allow ambulance staff to proceed in randomizing a patient using the physician-judgment consent method: an ambulance officer will sign on behalf of the patient, if there is no next-of-kin present and the patient is not competent to provide informed consent.

All competent randomized patients will be given a patient information sheet and informed consent form (PISCF) as soon as possible following their admission to hospital, ideally within the first 72 h. The PISCF will outline that the hospital (site) is “participating in research that is assessing early BP control delivered in ambulance on progression of the stroke and recovery” and that there is a need for data collection (in-hospital) and follow-up assessment at 3 months. The patient will have the opportunity to discuss and seek explanation from an approved clinician investigator familiar with the study protocol and use the locally approved consent process for collection of data (in-hospital and/or follow-up assessments).

In many patients with acute stroke, symptoms of the stroke can include diminished level of alertness, impaired language, confusion, and other cognitive deficits that render the patient unable to comprehend much of the information that is given to them. If a patient is not fully competent, the patient’s “surrogate” will be approached and will be provided with the PISCF to read and act on the patient’s behalf. A “person responsible” is the legally appointed guardian, their spouse or de-facto spouse or same sex partner; or if there is none, their unpaid carer; or if there is none, their relative or friend who has a close relationship with the person.

In situations where the patient is unable to provide consent and consent has been obtained from their surrogate, the patient will be made aware of this as soon as he/she is well enough, ideally before 7 days or their discharge from hospital, so that he/she will have an opportunity to discuss and seek explanation from a clinician investigator associated with the study. Patients will be given the opportunity to re-consent for the collection of their data (in-hospital and/or follow-up assessments) during their stay in hospital, or as soon as they are able to decide, according to the locally approved consent process.

If the patient is dying or remains unable to record their personal consent during follow-up, the consent given by the representative will stand, and study data will be retained (or removed, if appropriate). The reason for not being able to obtain the patient’s consent will be documented, dated, and signed, and included in the patient’s medical record for filing.

Withdrawal of consent: The PISCF provided to the patient and/or the next of kin or surrogate will clearly state that the patient can be withdrawn from the study at any time without prejudice and explanation. Such withdrawal should be documented in the patient’s file. If withdrawal of consent relates to the BP management alone, data collection can continue provided there is documentation of this fact in the patient’s files.

### Additional consent provisions for collection and use of participant data and biological specimens {26b}

Not applicable.

### Interventions

#### Explanation of the choice of comparators {6b}

The active comparator (intervention) is a treatment strategy of intensive BP lowering initiated in the ambulance in those participants with suspected stroke and hypertension to achieve a systolic BP target of < 140 mmHg within 30 min, and to maintain this BP level for the next 7 days, or at the time of hospital discharge should this occur earlier. The control comparator (control) is the treatment strategy according to local protocols based upon guideline-recommended BP management, both in the ambulance and the hospital. For those participants allocated to control group, BP lowering treatment can be considered for use in ambulance only in those patients with persistently very high systolic BP (e.g., ≥ 220 mmHg) or diastolic BP (e.g., ≥ 110 mmHg). After admission to hospital, patients in the control group should be treated based on a local guideline of each participating hospital, the features of which will be delineated.

#### Intervention description {11a}

The intervention, intensive BP management initiated in the ambulance, is to commence as early as possible after assessment of a patient, and to achieve a systolic BP level < 140 mmHg within 30 min, and to maintain this BP level for the next 7 days, or the time of hospital discharge should this occur earlier.

A recommended treatment regime is giving an IV bolus of 25 mg urapidil administered over 1 min, and another 25 mg urapidil bolus if the BP level persists > 150 mmHg after 5 min. Urapidil is a sympatholytic antihypertensive drug, which acts both as an α_1_-adrenoceptor antagonist and a 5-HT1A receptor agonist, and has a rapid onset (5 min, maximum at 15–30 min) and no effect on intracranial pressure (ICP). BP monitoring in the ambulance will occur every 5 min on electronic charts, delivered to the hospital staff. Allocation to early intensive BP lowering will be notified to hospital investigators as early as possible by the ambulance staff. Patients should keep a horizontal position while being transported to the hospital or other location. IV bolus (or maintenance infusion) treatment with urapidil will continue in the emergency department (ED), where it is anticipated that patients will stay (except for acute CT or MR imaging) until they are clinically stable, and that the target BP is achieved and maintained. BP lowering treatment chosen by the treating clinician will be continued in an acute stroke unit or other monitored facility, to maintain a systolic BP level < 140 mmHg for the next 7 days. Oral BP lowering agents (dependent upon local availability) can be used after a stable target BP level is reached, but it is expected that IV therapy will continue to be required during the initiation of oral antihypertensive therapy, to maintain the systolic BP levels of < 140 mmHg. A systolic BP < 130 mmHg is considered the threshold for cessation of therapy. Each site receives a standardized, stepped titratable, intravenous BP lowering protocol, based upon available medications, that is established in advance.

#### Criteria for discontinuing or modifying allocated interventions {11b}

The investigator must not deviate from the protocol, except where the patient/surrogate chooses to withdraw the consent of participation in this study. However, allocated management in either group should be discontinued or modified if any of the following occur: (i) a serious adverse event (SAE), which in the opinion of the investigator, is related to the trial protocol and (ii) the investigator feels that it is in the participant’s best interest.

Follow-up data will be collected for all participants, except those who specifically withdraw.

#### Strategies to improve adherence to the intervention {11c}

A process evaluation, designed to gain insights into the barriers and facilitators to change pre-hospital management and implementation of the intervention, will be undertaken through formative stakeholder interviews alongside with the trial. Preliminary findings have highlighted various barriers to BP lowering, whereby many ambulance doctors (i) are initially cautious with the treatment due to concerns over adverse effects, (ii) are not familiar with using IV urapidil, and (iii) have problems with continuity of the treatment during the transfer of care over to ED staff on presentation to hospital. To address these barriers, regular SAE reports related to intervention and DSMB recommendations are provided to both ambulance and hospital investigators, to inform them of the safety of intensive BP lowering in the hyperacute phase of stroke. Training on the administration and effects of urapidil and other rapid BP lowering agents are given to ambulance doctors. Regional coordination center (RCC) project staff will liaise with site investigators to establish the admission and treatment procedures in the ED at each site. Finally, ambulance and site investigators will be provided regular intervention quality reports during the study, as well as remote communication and on-site monitoring to improve the adherence to the intervention.

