## Assignment of interventions: blinding

### Who will be blinded {17a}

The treatment is open label to patients and investigators who need to provide BP management in the ambulance and at sites. All other investigators, statisticians and end-point assessors, who are trained to collect outcome measures by face-to-face visit or telephone at 3 months, are blind to the treatment allocation.

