### Composition of the data monitoring committee, its role, and reporting structure {21a}

#### DSMB

The DSMB is independent of the sponsor, and responsible for reviewing the safety, ethics, and outcomes of the study. During the period of patient recruitment, the DSMB monitors the primary, secondary, and safety outcomes for early dramatic benefits or potential harmful effects and provides reports to the TSC on recommendations to continue or temporarily halt recruitment to the study. The DSMB is governed by a Charter outlining responsibilities, procedures, and confidentiality and reviews the accumulating unblinded data at regular intervals (Additional file 2).

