## Discussion

INTERACT4 is a multi-center, ambulance-initiated, pre- and in-hospital-combined pragmatic clinical trial being conducted in China that aims to address ongoing uncertainties over the effectiveness and safety of early intensive BP lowering in patients with suspected stroke. The participation of a broad range of MEC administration systems in different medical resource settings across China will maximize the generalizability of the study results.

During the first year after the trial commenced, over 300 patients have been recruited at 30 hospitals in eastern (Shanghai) and western (Sichuan province) regions of China, demonstrating feasibility of the assessment and randomization systems, use of waiver of consent or brief consent, and implementation of the treatment in ambulance settings in both high- and low-medical resources regions. There have been several protocol deviations in the ambulance: (i) eligibility deviations, mostly from including randomized patients with an onset time beyond 2 h (mostly due to wake-up stroke) or with severe comorbid disease conditions, and (ii) intervention deviations that have included not providing BP lowering to patients allocated to the intensive group or giving BP lowering to those in control group. Short transportation times, for example averages of 15 and 20 min in Shanghai and Chengdu, respectively, are the main reason why ambulance doctors have limited time to collect baseline information or deliver treatment. However, such protocol deviations improved through 2021 after further training of investigators.

The COVID-19 pandemic caused a major challenge to the recruitment, mainly by adversely influencing the behavior of patients with suspected stroke symptoms [20]. More than half of the screen failure reasons were because of a presentation time beyond the inclusion criteria of 2 hours from symptom onset. Although COVID-19 was well controlled in China by mid-2020, these late-presenting patients (or their family members) indicated that they postponed calling the emergency hotline due to concerns of “getting infected” from being exposed at a “high-risk” hospital; their first reaction was to wait and hope that the symptom(s) would mitigate or disappear. Since the recruitment schedule was slower than planned across the two initial regional centers (Shanghai and Chengdu), the TSC decided to expand the study to other regions and hospitals in 2021.

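### Regular intervention-related SAE reports go to open-label enrolling and treating staff during recruitment, as reassurance about safety, with no stated limit on their content

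*Protocol article*

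**What the plan says.** The section on strategies to improve adherence {11c} reports early process-evaluation findings. One barrier is that many ambulance doctors "are initially cautious with the treatment due to concerns over adverse effects". In response, "regular SAE reports related to intervention and DSMB recommendations are provided to both ambulance and hospital investigators, to inform them of the safety" of intensive lowering in the hyperacute phase. The same section also plans training on urapidil and other rapid-acting agents, regular intervention quality reports, remote communication and on-site monitoring.

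On the recipients, the blinding section {17a} states: "The treatment is open label to patients and investigators who need to provide BP management in the ambulance and at sites". The eligibility section {10} adds that "the decision about a patient’s eligibility will be based on the interpretation of these criteria by participating ambulance staff".

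On accumulating data, the DSMB section {21a} says that the board works under a charter whose scope includes confidentiality, that it "reviews the accumulating unblinded data at regular intervals", and that its recommendations go to the steering committee. The SAE section {22} names the ethics committee (every 6 months) and the DSMB (at each meeting) as routine recipients of safety outcomes.

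**The concern.** Safety in all patients with suspected stroke is one of the listed research questions. The Introduction explains why it is open: an earlier pre-hospital trial of a glyceryl trinitrate patch found worse outcomes in patients with a final diagnosis of intracerebral hemorrhage. A running message to enrolling staff that the intervention is safe, drawn from this trial's own events, anticipates that answer.

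The recipients can act on the message. It could influence which patients they enter, how they manage blood pressure in controls, whether they record an event as an SAE, and whether they attribute it to the allocated management. Bias in SAE reporting or attribution would be hard to repair at analysis, because the analyst has only what was reported.

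**Working it through.** No figure in the plan decides this point. The check is mainly a comparison of sections, with one piece of arithmetic on how SAEs overlap with the primary outcome.

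**1. Timing and purpose.** The adherence section uses the present tense and describes a response to barriers found while the trial is under way. The Trial status section has enrolment running from March 2020 to December 2023. The reports are therefore regular, sent during recruitment, and have a purpose set in advance: to inform staff of safety.

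**2. What the recipients control.**
- Eligibility: ambulance staff interpret the criteria {10}.
- Treatment: the same open-label staff deliver either allocation in the ambulance. Hospital staff treat controls under local guidelines {6b}.
- Attribution: the SAE form records the principal investigator's opinion on causal relationship to the randomized group {22}. I read this as the site's principal investigator.
- Discontinuation: allocated management is stopped or modified if the investigator considers an SAE related to the trial protocol {11b}.

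**3. Two channels for safety information.** The DSMB and SAE sections route accumulating safety data to the DSMB and the ethics committee, with DSMB recommendations going to the steering committee. The adherence section adds a channel to sites. Passing on a DSMB recommendation is compatible with the first channel. Regular SAE reports specific to the intervention are not clearly so.

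**4. What the reports could contain.** The wording admits at least three readings:
- (a) notices of individual SAEs judged related to treatment;
- (b) counts pooled over both arms;
- (c) cumulative summaries for the intensive arm, by arm, or by relation to the intervention.

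Readings (a) and (b) are ordinary practice. Reading (c) is the problem. The article does not say which applies and sets no limit that excludes (c).

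**5. Overlap with the primary outcome.** Death is an SAE {22} and is also mRS 6 {12}. Under proportional odds, the treated proportion is p1 = 0.78·o / (1 + 0.78·o), where o = p0/(1 − p0). The common odds ratio and control distribution come from the sample size section {14}.
- The plan's own figure, mRS 3–6: o = 0.471/0.529 = 0.890; × 0.78 = 0.694; p1 = 0.694/1.694 = 41.0%. This matches the stated fall from 47.1% to 41.0%.
- Death, mRS 6: o = 0.130/0.870 = 0.149; × 0.78 = 0.117; p1 = 0.117/1.117 = 10.4%.

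Under the design assumptions, mortality would therefore be 13.0% against 10.4%. Under reading (c), a report split by arm would show part of the primary outcome. This illustrates what reading (c) could reveal; it does not show that such reports are sent.

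**6. What remains protected.** Allocation is concealed until the patient is enrolled {16b}. A change in whom staff enter therefore alters case mix, not comparability between arms. On outcome assessment, "All other investigators, statisticians and end-point assessors, who are trained to collect outcome measures by face-to-face visit or telephone at 3 months, are blind" to allocation, and the follow-up assessor is not involved in the patient's care {18a}. SAE reporting and attribution, and the blood pressure care given to controls, do not have the same protection.

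**The case against.** **The breach is inferred.** A reader might conclude that the practice breaks the confidentiality of accumulating data. The documents do not support that. No section says the reports are comparative, by arm or unblinded. Reports of single SAEs judged related to treatment are a fair reading, and neither those nor a DSMB recommendation to continue is a breach. This objection stands in full.

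**Report content belongs in documents not shown.** The DSMB charter covers confidentiality and may limit what sites receive. This stands as far as silence on format goes. It does not remove the point, which concerns a practice and purpose that the article states.

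**The harm is speculative.** The Discussion lists "giving BP lowering to those in control group" among deviations, and a reader might infer that safety messages caused it. The Discussion draws no such link. It lists the opposite deviation (intensive-group patients left untreated) alongside it, and says deviations improved after further training. Nor does anything suggest that an unfavourable report would stop recruitment outside the DSMB process. A reader might also put the stake as lost power through a diluted treatment contrast. The documents give no dilution rate, so any percentage would be arbitrary.

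**Safeguards exist.** SAEs are collected through set questions, reviewed by a medical monitor and centrally coded, and some reporting bias is inherent in an open-label design. This is correct and lowers the severity. However, the monitor and coder work from what the site reports, so these steps do not fully protect whether an event is reported or how the site attributes it.

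**Conclusion.** The point holds in a limited form. The adherence section, as worded, lets accumulating safety information on the intervention reach the staff who enrol, treat both arms and judge causality, and uses it as reassurance on an open trial question. That fits badly with the DSMB's role, but no breach of confidentiality is shown.

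The exposure is mainly SAE reporting and attribution, with co-management of controls and case mix behind it. The primary comparison is protected against selection by concealed allocation and against biased assessment by the blinded 90-day mRS. The size and direction of any effect cannot be derived from the documents.

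The conclusion assumes that the reports draw on this trial's own SAEs, as the wording indicates, and that no document outside the article already restricts their content. If the charter does so, only the article's wording needs correcting. Severity is minor to moderate: a cheap improvement, not an error that threatens the main result.

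**What to change.** Reword the sentence in the adherence section {11c} so that:
- during recruitment, sites receive only the DSMB's recommendation and SAE counts pooled over both arms;
- cumulative SAE summaries by arm, or by relation to the intervention, go only to the DSMB;
- individual-case SAE reporting, medical monitor review and ethics committee reporting under the SAE section {22} are unchanged.

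Address ambulance doctors' caution with the training and intervention quality reports already planned, and with evidence from outside the trial.

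The cost is one protocol sentence and a revised report template. Investigators lose one source of reassurance. Adherence support otherwise stays in place, and the Discussion itself reports that deviations improved after training.
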